### Outcomes {12}

The primary outcome of this study will be the infectious complication rate after PD. The secondary outcomes will be all postoperative complications; major complications (Clavien–Dindo grade > 3); clinically relevant POPF (CR-POPF); delayed gastric emptying (DGE); the length of hospital stay (LOS); time to functional recovery after surgery; serum levels of albumin, pre-albumin, and transferrin; the cost; side effects; and time to the introduction of adjuvant chemotherapy from surgery in patients with pancreatic cancer [14].

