## Data collection and management

### Plans for assessment and collection of outcomes {18a}

Case report forms are constructed as web-based forms (REDCap) and data entry will be conducted by surgeons or trained medical personnel. Baseline patient characteristics will include the age, sex, height, weight, hand grip strength, psoas mass index, comorbidity, preoperative diagnosis, preoperative treatment (neoadjuvant chemotherapy, antibiotics, biliary drainage, nutritional support), preoperative laboratory variables (white blood cell count, hemoglobin concentration, serum total protein, serum albumin, serum transferrin, serum pre-albumin, C-reactive protein), and the American Society of Anesthesiologists physical status.

Surgical data will include the surgical procedure, method of reconstruction, remnant pancreas texture, diameter of the main pancreatic duct, operation time, estimated blood loss, and need for a blood transfusion.

Postoperative data will include patients’ clinical conditions, morbidities and their severity, the mortality rate, length of hospital stay, time to functional recovery from surgery, laboratory data, cost, and any side effects. In patients with pancreatic cancer, the time to the introduction of adjuvant chemotherapy from surgery will also be measured. All patients will be followed up at each hospital for at least 90 days.

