## Statistical methods

### Statistical methods for primary and secondary outcomes {20a}

An intention-to-treat analysis will be conducted to compare primary and secondary outcomes between the EN group and the PN group. Differences between the groups of patients will be analyzed via Fisher’s exact test (as appropriate) for categorical data and by Student’s *t*-test for continuous variables. *P-*values of less than 0.05 will be considered statistically significant. Statistical analyses will be performed using SPSS version 28 (IBM Corp., Armonk, NY, USA).

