### Methods in analysis to handle protocol non-adherence and any statistical methods to handle missing data {20c}

No statistical methods will be used to compensate for missing data.

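### Time to adjuvant chemotherapy and time to functional recovery are left to a t-test that can only use patients who start or recover, which conflicts with the stated intention-to-treat analysis

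*Protocol article*

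**What the plan says.** Outcomes {12} of the protocol article lists among the secondary outcomes "the length of hospital stay (LOS); time to functional recovery after surgery", and also "time to the introduction of adjuvant chemotherapy from surgery in patients with pancreatic cancer".

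Statistical methods {20a} sets the analysis principle: "An intention-to-treat analysis will be conducted to compare primary and secondary outcomes between the EN group and the PN group". It then names two tests only: Fisher's exact test for categorical data, and the Student's t "test for continuous variables". No survival, competing-risk or rank method appears anywhere in the article.

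The section on non-adherence and missing data {20c} adds: "No statistical methods will be used to compensate for missing data".

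Plans for assessment and collection of outcomes {18a} gives the follow-up: "All patients will be followed up at each hospital for at least 90 days". Among the postoperative data it lists "morbidities and their severity, the mortality rate, length of hospital stay, time to functional recovery from surgery". It gives no rule linking death, non-recovery or never starting chemotherapy to the time outcomes, and no common cut-off day for them.

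**The concern.** A t-test needs one number per patient. Time to chemotherapy exists only for patients who start it, and time to functional recovery only for those who recover. With no other method named and no missing-data method allowed, the remaining patients have nothing to contribute and leave the comparison.

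The trial's hypothesis is that EN reduces infectious complications, which the Background calls sometimes life-threatening. Such complications can plausibly decide whether a patient recovers or starts chemotherapy at all. Restricting the analysis to those who do therefore conditions on something the intervention may change. Two consequences follow:

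- A benefit that takes the form of more patients starting or recovering is invisible to the test.
- If the additional starters begin late, they raise the mean in the better arm, and the estimate moves against it.

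**Working it through.** **Stated figures.** The article gives no start rate, recovery rate, time distribution, mortality or power for these outcomes, so there is no figure of its own to reproduce on this point. Its only calculated figure, 152 per group for 40% v 25%, does reproduce (two-sided 5%, 80% power, pooled variance):

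n = [1.96 × √(2 × 0.325 × 0.675) + 0.8416 × √(0.40 × 0.60 + 0.25 × 0.75)]² / 0.15² = 151.9, rounded up to 152.

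It concerns the primary endpoint and is untouched by this point.

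**Step 1: which method applies.** A time is not categorical, so Fisher's test does not apply to it. The t-test is the only other test in {20a}. A patient with no event has no value, and {20c} allows no method to supply one. The set analysed is then smaller than the intention-to-treat set promised in {20a}.

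**Step 2: bias in the mean (all inputs assumed).** PPN: 70% start, mean day 50. EN: the same 70% at mean day 50, plus 10% who would not have started under PPN and who start at day 85.

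- PPN mean among starters: 50.0 days.
- EN mean among starters: (70 × 50 + 10 × 85) / 80 = 54.4 days.
- Difference: 4.4 days against EN, although more EN patients start and none starts later than under PPN.

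In general the shift is e × (85 − 50) / (b + e), with b the base proportion and e the extra. With b = 65%, e = 5%, 10%, 15% and 20% give 2.5, 4.7, 6.6 and 8.2 days.

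**Step 3: would that difference be significant?** Assume 80 pancreatic-cancer patients per arm (half of 160), hence 56 PPN and 64 EN starters, and an SD of 18 days around each subgroup mean.

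- EN variance: 18² + 0.125 × 0.875 × 35² = 324 + 134 = 458.
- Standard error: √(324/56 + 458/64) = 3.6 days.
- t = 4.4 / 3.6, about 1.2.

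The point estimate is displaced, but the test would not be expected to reach significance.

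**Step 4: blindness to the proportion starting.** Simulation of 4,000 trials per row, 80 patients per arm, lognormal start times with mean 50 and SD 18 days, the same in both arms among starters (all assumed). The comparator is a rank test with non-starters placed last.

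| Start rate, EN v PPN | t-test in starters rejects | Rank test, all patients, rejects |
|---|---|---|
| 70% v 70% | 5% | 4% |
| 80% v 70% | 5% | 19% |
| 80% v 60% | 5% | 60% |
| 90% v 60% | 5% | 91% |

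The t-test stays at its nominal level even at a 30-point difference. The rank test's gain is not inflated error, as the first row shows.

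**Step 5: hospital stay.** Every patient who is discharged or dies in hospital has a stay, so hardly anyone drops out. The issue here is that an early death counts as a short stay. With an assumed mean of 25 days and deaths at day 8, mortality m changes the arm mean by m × (8 − 25): −0.17 day at 1% and −0.85 day at 5%.

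**The case against.** The strongest reply is that {20a} is one generic sentence that never mentions these outcomes, and that {20c} does not say non-starters are missing or will be removed. Censoring rules and the coding of deaths commonly belong in an analysis plan, and this article condenses a fuller protocol. Part of this stands. The removal of non-starters is an inference, though a firm one, since no other test is named and no missing-data method is allowed. The absence of coding detail is not criticised here. What remains is a stated test and a stated missing-data rule that do not suit these outcomes. An analysis plan could cure this only by replacing them.

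Several stronger readings are tempting and are not supported:

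- A reader might infer that early deaths count as favourable short times for all three time outcomes. That mechanism belongs to hospital stay alone; for the other two, a patient who dies before the event has no time. For hospital stay the assumed effect is under one day.
- A reader might take the 4.4-day example as a test result in favour of PPN. It is a constructed point estimate with t of about 1.2.
- A reader might conclude that times will often still be running at the end of follow-up. The article sets 90 days as a minimum and gives nothing from which to judge this.

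These are also only some of many secondary outcomes, which limits the consequence.

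**Conclusion.** The point holds for time to adjuvant chemotherapy and time to functional recovery. As written, the only available analysis compares starters with starters and recoverers with recoverers, which is not the intention-to-treat comparison the article promises. Its true size cannot be derived from the document. Under the assumed inputs above, the mean among starters moves 2.5 to 8.2 days against the arm in which more patients start, and the t-test has no sensitivity to the proportion starting. Hospital stay is a minor companion issue, at roughly 0.2 to 0.9 day for an assumed in-hospital mortality of 1% to 5%. The primary endpoint and the sample size are unaffected. The change is worth making before analysis, but the trial's main conclusion does not depend on it.

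**What to change.** Replace Student's t-test for these outcomes in {20a}, and state that a patient without the event is not a missing value under {20c}.

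- **Time to adjuvant chemotherapy and time to functional recovery:** analyse as time-to-event in all randomised patients (all randomised pancreatic-cancer patients for chemotherapy), with death as a competing event and censoring at one common fixed day. Day 90 is the latest day to which the article promises follow-up for everyone. Report cumulative incidence by arm with Gray's test or a stratified log-rank test, choosing one in advance, and the proportion started or recovered by the fixed day.
- **Hospital stay:** analyse as time to discharge alive, or by a rank test with in-hospital death ranked worst.

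The cost is mainly analysis wording. Results will no longer be differences in mean days. Dates of death and of last contact must be in the database: {18a} lists the times and mortality but does not mention these dates, so the sponsor should confirm that the case report form captures them.

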### Participant timeline {13}

The main timeline of this study is found in Fig. 2.

**Fig. 2 Fig2:**
[figure not shown]
The schedule of enrolment, interventions, and assessments

### Sample size {14}

The sample size was calculated for a 15% absolute reduction in the postoperative infectious complication rate in the EN group based on a postoperative complication rate of 40% in the PPN group [11]. To achieve 80% power and a 95% significance level, 152 patients are required in each group. To compensate for the loss of participants to follow-up (0.5%), we plan for 320 patients (160 in each group) to be included in the study.

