## Assignment of interventions: allocation

### Sequence generation {16a}

An electronic data capture system, Research Electronic Data Capture (REDCap), will be used to perform the randomization. Computerized stratified block randomization will be performed to determine the allocation to a treatment group in a 1:1 ratio. Stratification will be employed according to the hospital, age (≥ 70 or < 70), and preoperative diagnosis (pancreatic cancer or not) [3]. Data on all procedures will be managed by the Juntendo Clinical Research and Trial Center and will be unavailable to any researchers.

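### The sample size makes no allowance for the conservatism of Fisher's exact test, the only test named for categorical data: if it is used for the primary outcome, power is about 79% at the planned 160 per group, not 80%

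*Protocol article*

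**What the plan says.** The protocol article, Sample size {14}, describes the target effect as follows: "15% absolute reduction in the postoperative infectious complication rate in the EN group". The assumed control rate is 40%, so the comparison is 40% against 25%. The section concludes: "To achieve 80% power and a 95% significance level, 152 patients are required in each group". Enrolment is then rounded up to 160 per group, 320 in all, as an allowance for a 0.5% loss to follow-up. The section names neither a test nor a formula.

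Statistical methods for primary and secondary outcomes {20a} gives one generic rule for all categorical outcomes: "analyzed via Fisher’s exact test (as appropriate) for categorical data". On the threshold for P it says: "values of less than 0.05 will be considered statistically significant". The primary endpoint is binary (any infectious complication within 90 days of surgery) and has no test of its own. The article names no chi-square, stratified or regression analysis. It plans no interim analysis and no statistical compensation for missing data.

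**The concern.** A power statement belongs to a particular test. Fisher's exact test is conservative: because its p-values are discrete, it rejects a true null hypothesis in fewer than 5% of trials, and it pays for that in power. If the sample size formula ignores this and the analysis uses Fisher's test, the trial has less power than stated.

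The qualifier about appropriateness adds a second difficulty. It neither names an alternative test nor gives a rule for choosing one, so the text does not settle which test decides the primary outcome. In a borderline trial the choice matters. With 47/160 against 64/160 events, Fisher's test gives p = 0.060 and the uncorrected chi-square test gives p = 0.046. In an open-label trial meant to decide a standard of care, that choice should be fixed in advance.

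**Working it through.** **Inputs.** From Sample size {14}: control rate 0.40, experimental rate 0.25, power 80%, 160 enrolled per group, 0.5% loss. From Sequence generation {16a}: allocation is 1:1. From Statistical methods {20a}: alpha 0.05. Sidedness is not stated. I assume two-sided, because a one-sided calculation gives 120 per group and does not reproduce 152. I read the 95% significance level as alpha = 0.05.

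**Step 1: reproduce the plan's 152.** The mean rate is (0.40 + 0.25)/2 = 0.325, and the two variances sum to 0.40×0.60 + 0.25×0.75 = 0.24 + 0.1875 = 0.4275.

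- Pooled, uncorrected: [1.96·√(2×0.325×0.675) + 0.8416·√0.4275]² / 0.15² = 151.9, so **152**.
- Arcsine: h = 2(asin√0.40 − asin√0.25) = 0.322, and 2(1.96 + 0.8416)²/h² = 151.2, so **152**.
- Unpooled: (1.96 + 0.8416)² × 0.4275 / 0.15² = 149.1, so 150.
- Continuity-corrected, which approximates Fisher's test: 164.9, so 165.

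The stated figure therefore fits two formulas, and neither allows for Fisher's conservatism. Which one was used is an inference, since the article does not say.

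**Step 2: exact power of each test.** For each n per group, I summed the product of the two binomial distributions over every pair of event counts at which the test rejects (two-sided, p ≤ 0.05), with true rates of 0.40 and 0.25.

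| Analysed per group | Fisher's exact | Uncorrected chi-square |
|---|---|---|
| 152 | 76.8% | 80.3% |
| 159 | 78.7% | 81.9% |
| 160 | 79.0% | 82.2% |
| 163 | 79.9% | 83.0% |
| 164 | 80.1% | 83.2% |

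Fisher's test first reaches 80% at 164 per group, which is 164 − 152 = 12 more than stated (12/152 = 8%).

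**Step 3: what enrolling 160 recovers.** The stated loss leaves 160 × 0.995 = 159.2, so about 159 analysed per group. Fisher's shortfall is then 80 − 78.7 = 1.3 points, or 80 − 79.0 = 1.0 point with no loss. If all 8 extra patients per group are lost (8/160 = 5%), the analysed number returns to 152 and the shortfall is 80 − 76.8 = 3.2 points.

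**Step 4: type I error at 160 per group.** With a common event rate of 25%, 32.5% or 40%, Fisher's actual two-sided error is 3.7%, 3.8% and 3.7%. For the uncorrected chi-square test it is 5.1%, 5.0% and 4.8%.

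**Step 5: how often the choice matters.** At the design rates and 160 per group, the chi-square test is significant and Fisher's is not in 82.2 − 79.0 = 3.2% of trials. The reverse does not occur.

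**The case against.** The strongest reply is that the qualifier makes Fisher's test conditional. A common convention keeps it for sparse tables and uses chi-square elsewhere. With 160 × 0.25 = 40 and 160 × 0.40 = 64 events expected, the primary outcome is not sparse. On that reading the calculation and the analysis agree, and no power is lost. This stands as a possible reading, so the shortfall is conditional on Fisher's test being used. It does not close the point, because the text names no other test and gives no rule for leaving Fisher's.

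A second reply is that a journal article may leave the exact primary test to the full protocol or analysis plan. That would answer a complaint of omission. Here, however, the article does name a test, and the power beside it does not belong to that test.

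A third reply is that the gap is small beside the uncertainty in the assumed rates. With the same 15-point difference and 160 per group, Fisher's power is 80.5% if the control rate is 38% and 76.1% if it is 45%. This is correct and limits the weight of the point. The 47 against 64 table is likewise a chosen borderline case.

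Three stronger conclusions might be inferred, and the documents support none of them:

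- That 152 can come only from the uncorrected chi-square formula. The arcsine formula gives it too.
- That the trial certainly fails to deliver its power. This depends on which test is used.
- That the result would be invalid. Fisher's test keeps type I error below 5%, so a positive finding would stand.

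**Conclusion.** The point holds as a conditional mismatch of minor to moderate weight. It rests on a two-sided 5% level, true rates of 40% and 25%, equal groups and an unstratified Fisher's test for the primary outcome. At the enrolment actually planned, the loss is about 1 point of power. The 3-point figure applies only if dropout uses up the whole margin, which means 5% loss against the stated 0.5%. If an uncorrected chi-square test was intended, the stated 80% is sound and only the wording needs repair. Either way, the article does not tie its power claim to one fixed test of the primary endpoint.

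**What to change.** Before any comparative data are seen, add one sentence to Statistical methods {20a} naming a single primary test that is consistent with the calculation. Two choices are suitable:

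- the uncorrected chi-square test, with exact power of 80.3% at 152 and 82.2% at 160 per group;
- a Mantel-Haenszel test stratified by the randomisation factors (hospital, age, preoperative diagnosis). Its power was not computed here, because the article gives no event rates by stratum.

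State the test and its two-sided level in Sample size {14} as well. Keep Fisher's exact test for sparse secondary outcomes, and remove the qualifier for the primary outcome. This costs a sentence in each section and no extra patients.

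If Fisher's test is kept for the primary outcome, restate power as about 77% at 152 and 79% at 160 analysed per group. Holding a full 80% would instead need 164 evaluable per group. At the stated 0.5% loss, that is 164/0.995 = 164.8, so 165 per group or 330 in total, which is 10 more than planned.

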### Recruitment {15}

This study will be conducted at six Japanese high-volume centers. The surgeons at each hospital will provide patients with adequate information about the study.

## Assignment of interventions: allocation

### Sequence generation {16a}

An electronic data capture system, Research Electronic Data Capture (REDCap), will be used to perform the randomization. Computerized stratified block randomization will be performed to determine the allocation to a treatment group in a 1:1 ratio. Stratification will be employed according to the hospital, age (≥ 70 or < 70), and preoperative diagnosis (pancreatic cancer or not) [3]. Data on all procedures will be managed by the Juntendo Clinical Research and Trial Center and will be unavailable to any researchers.

### Concealment mechanism {16b}

The result of the allocation will be shown via the REDCap system in each hospital.

### Implementation {16c}

The allocation sequence, enrolment of participants, and assignment of participants to interventions will be generated by the Juntendo Clinical Research and Trial Center.

## Assignment of interventions: blinding

### Who will be blinded {17a}

Data analysts will be blinded. Trial participants and researchers will not be blinded to the group allocations because the percutaneous tube for EN will be placed only in patients allocated to the EN group.

### Procedure for unblinding if needed {17b}

Not applicable.

## Data collection and management

### Plans for assessment and collection of outcomes {18a}

Case report forms are constructed as web-based forms (REDCap) and data entry will be conducted by surgeons or trained medical personnel. Baseline patient characteristics will include the age, sex, height, weight, hand grip strength, psoas mass index, comorbidity, preoperative diagnosis, preoperative treatment (neoadjuvant chemotherapy, antibiotics, biliary drainage, nutritional support), preoperative laboratory variables (white blood cell count, hemoglobin concentration, serum total protein, serum albumin, serum transferrin, serum pre-albumin, C-reactive protein), and the American Society of Anesthesiologists physical status.

Surgical data will include the surgical procedure, method of reconstruction, remnant pancreas texture, diameter of the main pancreatic duct, operation time, estimated blood loss, and need for a blood transfusion.

Postoperative data will include patients’ clinical conditions, morbidities and their severity, the mortality rate, length of hospital stay, time to functional recovery from surgery, laboratory data, cost, and any side effects. In patients with pancreatic cancer, the time to the introduction of adjuvant chemotherapy from surgery will also be measured. All patients will be followed up at each hospital for at least 90 days.

### Plans to promote participant retention and complete follow-up {18b}

Medical interviews and laboratory examinations will be booked for all patients at each hospital.

### Data management {19}

Every patient will be coded with an individual randomization number at each hospital and their data will be collected via an electric data system (REDCap). To enhance data quality, REDCap is designed so that researchers could not enter non-realistic values. Before data analyses, all data will be checked by an experienced research administrator independent of analyses.

### Confidentiality {27}

The form used to code patients will be stored in a locked cabinet with logged access only available to the researchers and administrators responsible for the study.

### Plans for collection, laboratory evaluation, and storage of biological specimens for genetic or molecular analysis in this trial/future use {33}

Not applicable.

## Statistical methods

### Statistical methods for primary and secondary outcomes {20a}

An intention-to-treat analysis will be conducted to compare primary and secondary outcomes between the EN group and the PN group. Differences between the groups of patients will be analyzed via Fisher’s exact test (as appropriate) for categorical data and by Student’s *t*-test for continuous variables. *P-*values of less than 0.05 will be considered statistically significant. Statistical analyses will be performed using SPSS version 28 (IBM Corp., Armonk, NY, USA).

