**Methods:**

A multicenter (six hospitals), open-label, randomized controlled trial will be started in July 2022. A total of 320 patients undergoing open PD will be randomly assigned to an EN group or a peripheral parental nutrition (PPN) group in a 1:1 ratio. The stratification factors will be the hospital, age (≥ 70 or not), and preoperative diagnosis (pancreatic cancer or not). In the EN group, enteral nutrition will start on postoperative day (POD) 1 at 200–300 ml/day via the percutaneous tube placed operatively. The volume of the diet will be increased to 400–600 ml/day on POD 2 and depend on the surgeon’s decision from POD 3. In the PPN group, PPN will be delivered after surgery. In both groups, oral feeding will start on POD 3. Each treatment will be finished when patients’ oral food intake reaches 60% of the nutritional requirement (25–30 kcal/day). The primary endpoint will be the occurrence of postoperative infectious complications within 90 days of surgery. The secondary endpoints will be all complications, including major ones such as Clavien–Dindo grade 3 or more and clinically relevant postoperative pancreatic fistula. Data will be analyzed per the intention to treat.

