## Discussion

In this RCT, we evaluate whether EN reduces the infectious complication rate after PD under the ERAS protocol. Patients start clear water without restrictions and solid food on POD 3, which is reasonable timing, as the ERAS protocol [15]. PPN combined with the early restart of oral intake is used as standard treatment. TPN will be used when patients in the PPN group could not get sufficient oral intake until POD 14 because TPN in the immediate postoperative period could increase the infectious complication rate and the overall morbidity according to the American Society for Parenteral and Enteral Nutrition (ASPEN) and European Society for Clinical Nutrition and Metabolism (ESPEN) guidelines [16, 17]. We have defined seven diseases as postoperative infectious complications (the primary endpoint) according to previous studies [3, 18, 19]. The diagnostic criteria for each complication are also clearly defined. On the other hand, inflammatory disorders of unknown causes will not be counted as infectious complications [20]. These definitions will provide clear evidence of the benefit of EN for patients undergoing PD. EN is delivered via percutaneous tubes placed operatively to increase its feasibility and accurately judge its efficacy. In a previous study conducted in France, EN delivered via nasojejunal tubes resulted in a high failure delivery rate of 37%, which made it difficult to assess the effect of EN [1]. Moreover, a previous systematic review reported that EN via percutaneous tubes was superior to that via nasojejunal tubes in the aspect of improving postoperative outcomes after PD [21]. The amount of feeding will be gradually increased to monitor the tolerance and to avoid patient drop-out. Patient allocation is determined by the hospital, age, and preoperative diagnosis. A patient’s age and preoperative diagnosis (pancreatic cancer or not) are reported to be associated with postoperative infectious complications [3]. We recognize that preoperative biliary drainage is a major risk factor for postoperative infectious complications; so, preoperative biliary drainage will serve as a factor in the planned subgroup analysis.

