A potential limitation of this study is that we will not be able to perform a double-blind study, and this limitation could affect our results; however, it could be minimized by using strictly defined diagnostic criteria for infectious complications and the Clavien–Dindo grading system. Another limitation is that concomitant treatments could affect some outcomes. However, no treatments have strong evidence to mitigate the primary outcome of our study. Although our study will be performed under the ERAS protocol, the ERAS protocol is not completely the same in six hospitals because each hospital has its own ERAS protocol. However, we have an agreement in the majority of current ERAS items such as preoperative smoking and fasting, epidural analgesia, postoperative glycaemic control, early removal of drains, early and scheduled mobilization, and early diet from postoperative day 3 [15].

This trial is the first large-scale, well-designed RCT to investigate whether EN is beneficial for patients undergoing PD under the ERAS protocol. According to the results of this study, either EN or PPN would be adopted as standard nutritional support for patients undergoing PD.

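### Randomisation is stratified by hospital, age and diagnosis, but the primary comparison is a crude Fisher test: valid, yet conservative, and it gives up a few points of power that an adjusted analysis would recover

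*Protocol article*

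**What the plan says.** Protocol article, Sequence generation {16a}: "Stratification will be employed according to the hospital, age (≥ 70 or < 70), and preoperative diagnosis (pancreatic cancer or not"). With six hospitals this makes 6 × 2 × 2 = 24 strata, filled by blocked 1:1 allocation. The Discussion explains that age and diagnosis were chosen because they have been reported to relate to infectious complications after surgery, which is the primary outcome.

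Statistical methods {20a} sets an intention-to-treat comparison and gives Fisher's "exact test (as appropriate) for categorical data", with a t-test for continuous variables. The article names no stratified test, regression model or covariate, and hospital enters no analysis.

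On drainage, the Discussion states: "We recognize that preoperative biliary drainage is a major risk factor for postoperative infectious complications". It is recorded at baseline ({18a}) but used only as a subgroup factor ({20b}).

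**The concern.** Blocking within strata that predict the outcome makes the arms more alike than simple randomisation would, so the treatment difference varies less from trial to trial. A crude two-by-two test does not know this. It uses the full binomial variance, so it rejects too rarely under the null and loses the precision that stratification was meant to give. Fisher's test adds conservatism of its own because it is discrete. At stake are a few points of power in a trial sized at 80%, and an analysis that does not follow its design. Drainage is a separate matter: the protocol regards it as strongly prognostic, yet the main comparison makes no use of it.

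**Working it through.** **1. The plan's own figure.** Sample size {14} assumes a 40% risk on PPN and a risk 15 points lower on EN, and concludes: "To achieve 80% power and a 95% significance level, 152 patients are required in each group". I take alpha as 0.05 two-sided, which reproduces the figure. With p1 = 0.40, p2 = 0.25 and mean 0.325:

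n = [1.960·√(2·0.325·0.675) + 0.842·√(0.40·0.60 + 0.25·0.75)]² / 0.15² = (1.298 + 0.550)² / 0.0225 ≈ 151.9, so 152 per group.

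This is the uncorrected two-proportion formula. It allows neither for Fisher's discreteness nor for strata.

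**2. Fisher's test without strata, by full enumeration.** Power is 76.8% at 152 per group and 79.0% at 160; 80% needs 164. True size at 160 per group is 3.7–3.8%. The uncorrected formula gives 82.0% at 160. Part of the conservatism therefore has nothing to do with stratification.

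**3. Why the strata matter.** For stratum risks p_s with mean p, p(1 − p) = mean[p_s(1 − p_s)] + Var(p_s). The crude test uses the left side; stratified blocking removes most of the last term. If Var(p_s) = 0, nothing is gained.

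**4. Separating the two effects by simulation.** The documents give no prognostic strengths, factor prevalences or block size, so these are assumed: 320 patients, 24 strata, blocks of 4, marginal risks 40% v 25%. Crude chi-square is the comparator that isolates the strata. The Mantel-Haenszel (CMH) statistic is Σ(a_s − k_s·m_s/n_s) divided by the square root of Σ k_s(n_s − k_s)m_s(n_s − m_s)/[n_s²(n_s − 1)], where stratum s has n_s patients, k_s on EN, m_s events and a_s EN events.

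| Power | Fisher | Crude chi-square | CMH | Discreteness | Strata |
|---|---|---|---|---|---|
| Mid-strength, run 1 (hospital SD 0.4; log-odds +0.4 age, −0.7 diagnosis) | 80.9% | 83.0% | 84.3% | 2.1 | 1.3 |
| Mid-strength, run 2 | 82.1% | 84.1% | 85.0% | 2.0 | 0.9 |
| Stronger, run 2 | 81.4% | 83.4% | 86.3% | 2.0 | 2.9 |

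Run 1 with stronger effects (SD 0.6, +0.7, −1.1) gave 83.3% for chi-square and 86.6% for CMH, a strata share of 3.3. Total gaps between Fisher and CMH are 3.4, 2.9 and 4.9 points. Type I error at mid-strength was 3.4%, 4.3% and 5.0% (run 1) and 3.6%, 4.3% and 4.8% (run 2) for Fisher, chi-square and CMH. Simulation error on power is about 0.5 points in run 1 (6,000 replicates).

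**5. Adding drainage.** Further runs used 4,000 replicates and 50% prevalence for each two-level factor. Assumed odds ratios for age, diagnosis and drainage, and hospital SD, were: weak 1.3, 1.5, 1.5, 0.2; moderate 1.5, 2, 2, 0.4; strong 2, 3, 3, 0.6. Two decimals are shown only so that differences can be followed.

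| Power, % | Fisher | CMH | Logistic, strata factors | Same plus drainage | Gain from drainage | Fisher type I |
|---|---|---|---|---|---|---|
| None | 80.55 | 82.00 | 82.75 | 82.63 | −0.12 | 4.73 |
| Weak | 81.08 | 83.15 | 83.78 | 83.93 | 0.15 | 3.98 |
| Moderate | 81.28 | 84.58 | 85.13 | 86.10 | 0.97 | 3.73 |
| Strong | 81.15 | 86.50 | 86.83 | 89.28 | 2.45 | 2.75 |

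The standard error of a 5% rejection rate is √(0.05·0.95/4000) = 0.34 points. In the no-effect null run every method came out high (adjusted tests 6.0–6.2%), so the exact 3.7–3.8% in step 2 is the better guide to Fisher there. Elsewhere the adjusted tests lay between 4.8% and 5.7%. With no prognostic effect the Fisher–CMH gap is 82.00 − 80.55 = 1.45 points, and by step 3 none of it can come from the strata.

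**6. Chance imbalance in drainage.** At an assumed 50% prevalence and 160 per arm, the standard error of the prevalence difference is √(2·0.25/160) = 0.056, so the 95% range is ±0.11. Multiplied by an assumed 10–20 point risk difference, the estimate moves by about ±1 to ±2 points, against a 15-point target.

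**The case against.** The crude test controls the false-positive rate, matches the unadjusted formula behind the sample size, and in these simulations stays at about 81–82% power when prognostic effects are present. All of that stands. Every prognostic strength is assumed, and the benefit shrinks to almost nothing if the factors do not predict outcome; that also stands and limits how firmly the size can be stated.

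Three stronger readings are tempting, and the documents do not support them.

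- A reader might infer that ignoring the strata invalidates the test. It errs the other way: it rejects too seldom.
- A reader might charge the whole 3–5 point gap to the strata. About 2 points are Fisher's discreteness, present in any unstratified two-arm trial.
- A reader might infer that drainage imbalance biases the result. Under randomisation, chance imbalance in an unstratified covariate is random error already covered by the test. Drainage was not a stratification factor, so the randomisation scheme does not itself call for adjusting for it.

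Hospital differences should not be pressed too far either. The Discussion says "the ERAS protocol is not completely the same in six hospitals because each hospital has its own ERAS protocol", but adds that the hospitals agree on most items. The choice of enteral formula belongs to the EN arm's intervention and is not a baseline prognostic factor.

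A separate analysis plan could hold an adjusted model. The article nevertheless positively names a crude test. The words in brackets after it allow at most a choice among crude tests, which could recover the discreteness loss but not the strata share. The subgroup analyses address effect modification and do not adjust the main comparison.

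**Conclusion.** The point holds as one of efficiency and of matching analysis to design, not of validity. Under assumed moderate to strong prognostic effects, crude Fisher has a type I error of about 3–4% and gives up about 3–5 power points against a stratified test at the same 320 patients: about 2 from discreteness and 1–3 from ignoring the strata. Under weak effects the total is about 2 points (83.15 − 81.08). Adjusting for drainage adds about 0–2 points more. These sizes rest on assumed effect strengths, prevalences and blocks of 4. The mismatch between the stratified randomisation and the crude test is read directly from the text.

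**What to change.** In Statistical methods {20a}, name one adjusted primary analysis: logistic regression of 90-day infectious complication on treatment, with main effects for hospital, age 70 or over, pancreatic cancer and preoperative biliary drainage. Report a standardised risk difference with 95% CI, which keeps the result on the absolute scale used for the sample size. State that drainage is included for precision and protection against chance imbalance.

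A Mantel-Haenszel test and risk difference over the randomisation factors is an acceptable alternative, but it does not adjust for drainage, and 24 cells average only 320/24 ≈ 13 patients. Main effects are therefore more practical. Keep the crude comparison as supportive.

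The cost is a few sentences. The covariates are already collected, the model runs in SPSS, and the sample size need not change. No interim analysis is planned, so the change can be dated before any unblinded comparison; made after results are seen, it would look data-driven.
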